### Aim 1: Testing the Effectiveness of the Novel Support-Moms Intervention in a Randomized Controlled Trial

We will enroll a cohort of 824 adult pregnant individuals with gestational ages ≤20 weeks at enrollment (determined by last normal menstrual period or ultrasound scan where available). Consenting participants will be randomized 1:1 at enrollment to standard of care (Ministry of Health [MOH] guidelines–based routine care and information giving, n=412, 50%) versus the Support-Moms (intervention) group (n=412, 50%). We will identify, screen, and enroll people through the existing CHWs or VHT structure from areas within a 10 km radius of all publicly funded maternity centers across Mbarara and Mitooma districts, who have not yet presented for ANC by the beginning of their second trimester. We will power the study to test the superiority of the Support-Moms intervention for our primary effectiveness outcome: HCP-led skilled birth delivery. Secondary outcomes will include (1) number of ANC visits, (2) institution-based delivery, (3) SS, (4) mode of infant delivery, (5) all deaths (maternal, fetal, and newborn), (6) preterm birth, (7) birth weight, (8) breastfeeding, (9) completion of postnatal care, and (10) complications of pregnancy and childbirth (eg, obstructed labor, ruptured uterus, need for neonatal or maternal resuscitation or assisted ventilation, severe preeclampsia or eclampsia, postpartum hemorrhage, maternal or newborn sepsis, and other infections).

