### Aim 1: Analysis Plan and Sample Size Calculations

We will first summarize health-related and sociodemographic data between arms. For our primary effectiveness outcome, HCP-led skilled birth delivery, we will fit a multivariable logistic regression model, with study arm as the predictor of interest, and age, high-risk pregnancy, and health facility at enrollment as a priori additional variables in the model, due to their strong association with the selected outcome [70,90,91]. In our primary intention-to-treat model, we will consider women with missing outcome data, after home visits and next of kin interviews, as presumed to have not received skilled birth (ie, there will be no missing outcome data in our primary analysis). In sensitivity analyses, we will (1) repeat the analysis after excluding women with missing outcome data and (2) include additional potential confounders in the model that may have persisted despite individual randomization (eg, number of previous deliveries at a facility, socioeconomic status, distance to facility, history of facility delivery, food insecurity, alcohol use, and depression). Although not designed to detect a difference, we will also explore additional secondary outcomes, including (1) number of ANC visits completed, (2) mode of infant delivery, (3) institution-based delivery, (4) presence of one or more birth complications, (5) child mortality, (6) maternal mortality, (7) preterm birth, (8) birth weight, (9) completion of postnatal care, (10) SS, and (11) initiation of breastfeeding. Both our pilot data and other similar studies estimate that 70% of the women in Uganda deliver with a skilled attendant [15,48,49]. Finally, we will explore the role of SS as a moderating effect of the intervention through a prespecified stratified analysis among women in the upper versus lower half of SS in the cohort, as measured by the Duke-UNC Functional Social Support Scale [64]. To test our primary effectiveness hypothesis, allowing for a 2-sided type I error of 5%, 90% power, and assuming a 5% loss to follow-up, we will require 824 participants to detect a 10% difference in HCP-led skilled birth delivery between arms. Data analysis will be conducted using Stata (version 17; StataCorp LLC). The findings will be presented as descriptive statistics, scatter plots, and graphs; statistical significance will be considered at *P*≤.05. While we will ensure completed data are collected through timely cleaning and REDCap prompts, we will still be able to detect the same effect in the primary outcome with the power of 85% in the unlikely event that we lost up to 18% of the records due to missing data.

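### The stated 90% and 85% power belong to an analysis that drops lost women, not to the declared primary analysis, which counts them as having no skilled birth

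*Protocol article*

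**What the plan says.** All of the relevant text is in the protocol article, section Aim 1: Analysis Plan and Sample Size Calculations.

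- **Primary rule.** In the intention-to-treat logistic model, women whose outcome is still unknown after tracing are counted as not having had a skilled birth. The article draws the consequence itself: "there will be no missing outcome data in our primary analysis". Leaving these women out is the first sensitivity analysis.
- **Main power statement.** "90% power, and assuming a 5% loss to follow-up, we will require 824 participants to detect a 10% difference" in skilled birth between arms, at a two-sided 5% level.
- **Control rate.** "Both our pilot data and other similar studies estimate that 70% of the women in Uganda deliver with a skilled attendant".
- **Contingency statement.** If up to 18% of records were lost, "we will still be able to detect the same effect in the primary outcome with the power of 85" per cent.

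**The concern.** Loss to follow-up acts on power in two different ways, depending on how lost women are handled. If they are excluded, the sample shrinks and the 10-point difference stays intact. If they are kept and counted as failures, the sample stays at 412 per arm, but both proportions, and hence their difference, shrink by the missing fraction. The second effect costs more power for the same amount of loss.

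The article declares the second handling as primary but appears to compute power under the first. If so, its two planning figures do not describe the test on which the trial will be judged. The 18% statement matters most. It tells the reader that a substantial loss of data is tolerable, and it would shape how a null result is read if such a loss occurred.

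**Working it through.** **Inputs from the article.** Two-sided α = 0.05; control rate 70%; difference 10%, read as absolute (70% vs 80%, the reading that reproduces 824); 1:1 allocation, 412 per arm; loss of 5% and 18%.

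**Formulas** (pooled variance, no continuity correction), with d = p2 − p1 and p̄ the mean of p1 and p2:

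- n per arm = [1.96·√(2p̄(1−p̄)) + 1.2816·√(p1(1−p1)+p2(1−p2))]² / d²
- power = Φ{ [d·√n − 1.96·√(2p̄(1−p̄))] / √(p1(1−p1)+p2(1−p2)) }

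**Step 1: reproduce the sample size.** At 70% vs 80% the two square roots are 0.6124 and 0.6083. Then n = (1.2002 + 0.7795)² / 0.01 = 391.9, so 392 per arm and 784 in total. Multiplying by 1.05 gives 823.2, so 824; dividing by 0.95 gives 826. The stated 824 is reproduced.

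**Step 2: reproduce the stated powers by dropping lost women.**

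- 5% dropped: n = 412 × 0.95 = 391.4. (1.9784 − 1.2002)/0.6083 = 1.279; power 90.0%.
- 18% dropped: n = 412 × 0.82 = 337.8. (1.8380 − 1.2002)/0.6083 = 1.049; power 85.3%.

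Both match the article.

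**Step 3: apply the primary rule.** Keep 412 per arm and multiply both rates by (1 − missing). This assumes equal loss by arm, and that lost women would otherwise have had the same 70% and 80% rates as the others.

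- 5% missing: 66.5% vs 76.0%, d = 9.5 points. (1.9283 − 1.2545)/0.6365 = 1.059; power 85.5%.
- 18% missing: 57.4% vs 65.6%, d = 8.2 points. (1.6644 − 1.3487)/0.6857 = 0.460; power 67.7%.

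**Step 4: does the result depend on the formula?** Unpooled variance gives 85.8% and 68.0%. A simulated unadjusted logistic Wald test gives 85.6% and 67.7%. With a continuity correction the figures are 83.7% and 65.1%. The gap remains in each case.

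**Step 5: how far does it depend on the assumptions?**

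| Women still missing after tracing | Lost women have the same rates as others | Lost women have half the overall rates |
|---|---|---|
| 0% | 91.4% | 91.4% |
| 1% | 90.3% | not needed |
| 2.5% | 88.6% | not needed |
| 5% | 85.5% | 88.6% |
| 18% | 67.7% | 80.2% |

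In the last column, 70% and 80% are the rates among all randomised women, and lost women have 35% and 40%. The analysed rates are then 0.70 − 0.35m and 0.80 − 0.40m for missing fraction m: 68.25% vs 78.0% at 5%, and 63.7% vs 72.8% at 18%. In the extreme case where no lost woman had a skilled birth and the overall rates are still 70% and 80%, the coding is correct, nothing is diluted, and power is 91.4% at either level of loss.

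**The case against.** The strongest reply is that nothing has been miscalculated: 824, 90% and 85% all reproduce. That stands. The fault is a mismatch between the basis of the power figures and the analysis rule.

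Second, the 5% is loss to follow-up, whereas the failure rule applies only to women whom home visits and relatives could not account for. The Data Collection section for aim 1 sets out that tracing, including whether a skilled attendant was present, and the Results section reports no loss so far, with 124 women exited. This also stands in part. The 85.5% is the figure if tracing recovers none of the 5%, and the practical effect at that level may be small.

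Third, the 18% could be read as incomplete forms, such as missing covariates, which would drop out of a multivariable model whatever the outcome rule. That fits the neighbouring remark about data cleaning. It fits less well with a sentence that is about detecting the same effect in the primary outcome, and the article does not say that only covariates are meant.

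Fourth, the plan presumes that lost women had no skilled birth. To the extent that this is true, the dilution is smaller, as step 5 shows. This stands, and it is why a range is needed.

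Fifth, adjustment for prognostic covariates is ignored here. The article gives no figures from which its effect could be worked out, and its own power figures reproduce without it.

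A reader might go further and infer that the trial simply has 86% and 68% power, that 824 is wrong, or that the primary missing-data rule must be replaced. The documents support none of these. The lower powers are conditional, the sample size follows from its inputs, and the choice of missing-data rule is a separate trade-off.

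**Conclusion.** The point holds as an inconsistency within one section. The stated 90% and 85% are powers of the complete-case sensitivity analysis, not of the declared primary analysis. Under the primary rule, power is about 86% at 5% residual missing and about 68% at 18%. In the 18% case the risk of missing a true effect is then about 32% (100 − 68) instead of the implied 15%.

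These figures assume a 70% to 80% absolute increase, equal loss by arm, the 5% and 18% still missing after tracing, lost women with the same underlying rates as the others, and no gain from covariate adjustment. Relaxing the tracing or rate assumption narrows the gap. At 5% the shortfall is at most modest and may vanish; at 18% it is substantial unless lost women really had few skilled births.

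**What to change.** In the section Aim 1: Analysis Plan and Sample Size Calculations:

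1. Label the 90% (5% lost) and 85% (18% lost) figures as applying to the complete-case sensitivity analysis.
2. State power for the primary rule: about 86% at 5% and about 68% at 18% of women still missing after tracing.
3. Give the assumptions (70% vs 80%, equal loss by arm, lost women otherwise like the rest) and a range, for example 90.3% at 1% and 88.6% at 2.5% residual missing, and 88.6% and 80.2% at 5% and 18% if lost women have half the overall rates.
4. Say whether the 18% refers to missing outcomes, missing covariates or both.

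This is a change of wording. It needs no extra participants and no change to the primary analysis. The only downside is a less favourable stated power.

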
### Aim 2: Evaluating Intervention Implementation

We will evaluate intervention implementation using the framework by Proctor et al [66] (Figure 1) and plan for future scale-up per the CFIR [67] (Table 3). While the effect of the Support-Moms intervention on HCP-led skilled birth delivery, ANC attendance, and other secondary outcomes in aim 1 is critical, the translation of its potential benefit into routine care impact requires understanding the implementation process. We chose the evaluative framework by Proctor et al [66] because it consists of essential implementation science outcomes with attention to both services and clients, which will be critical for uptake and long-term use of Support-Moms in routine care (Figure 1 and Table 4). Then, we will consider and refine implementation strategies for future scale-up using the CFIR as a determinant implementation science framework (Table 3) [67].

**Table 3 table3:** Consolidated Framework for Implementation Research (CFIR) constructs that will guide data collection on intervention challenges, facilitators, and potential strategies by care users, health care providers (HCPs), and payers and managers.

CFIR construct	Interview topic	Possible questions to elicit implementation strategies from users and implementers
Intervention characteristics	Intervention-setting fitness, automation, and auditing	On the basis of the reported or presented acceptability, effectiveness, patient centeredness, satisfaction, and function outcomes, how can the intervention be improved for increased implementation?
Outer setting	Existing policy, resources, and MOH^a^ willingness and capacity to support increased demand for services and adopt the intervention	On the basis of the presented adoption, penetration, and other outcomes, as well as existing policies and resource commitments, what rollout strategies will be most effective in overseeing intervention implementation?
Inner setting	Facility adaptive reserve, leadership endorsement, and resource reallocation	On the basis of the identified cost-effectiveness, how can existing resources be reallocated to promote intervention uptake?
Individual characteristics	Patient centeredness, support, and community referrals	On the basis of acceptability, satisfaction, and function, what potential support will be needed for individuals using Support-Moms to improve uptake, enthusiasm, and retention?
Implementation process	Experience of HCPs on app enrollment, patient interaction, and increased demand and implementer’s intention to “try,” budgeting, sustainability, timing, execution, and scale-up	Explore implementers’ support and satisfaction of the app to improve service use; approaches to publicizing and dissemination; engaging CHWs^b^, focal HCPs, and social supporters as champions; long-term funding, potential impact; and “leading” or “lagging” indicators of the implementation success

^a^MOH: Ministry of Health.

^b^CHW: community health worker.

**Table 4 table4:** Application of the framework by Proctor et al [66] to evaluate implementation, service, and client outcomes.

Outcomes and domain		Specific intervention measures	Data source
**Implementation outcomes**			
	Acceptability	Reported ease of use and performance expectancy, effort expectancy, social influence, facilitating conditions, self-efficacy, and behavioral intention to use the app in the future Overall user acceptability per the tool by Weiner et al [92] Qualitative: For example, participants: How was it for you to use these SMS, messaging, or calls? and HCP^a^: How was it for you using the messaging app?	Exit interviews Exit questionnaire
	Adoption	Initiation and use of the app over time Percentage of eligible and participating social supporters	mHealth^b^ platform Study records
	Appropriateness	Relevance (for setting) and compatibility Overall appropriateness with the tool by Weiner et al [92] for both HCPs and end users Qualitative: For example, participants: What happened when you received SMS or voice calls? and HCP: What happened or what did you observe when you enrolled people on the app?	Exit interviews Exit questionnaire
	Cost	Refer to aim 3: Evaluating the Cost and Cost-Effectiveness of Implementing the Support-Moms Intervention Into Routine Care and Its Implication for Sustainability section	Refer to aim 3
	Feasibility	Percentage of users willing to participate; percentage of women, spouses, and social supporters meeting eligibility criteria; recruitment or participating rates, and reason for not participating. We will use the tool by Weiner et al [92] to measure feasibility for both HCPs and end users.	mHealth platform Study records Exit questionnaire
	Fidelity	Percentage of HCs^c^ with capacity and integrity to deliver intended service (ANC^d^, skilled deliveries, and admissions), percentage of accessible cell phones, and percentage of messages automatically sent out Percentage of SMS or voice calls received by the participant over anticipated per protocol Percentage of network, dead battery, phone losses, and phone functionality issues encountered	Study records mHealth platform Facility audits
	Penetration	Number and type of HCs and HCPs engaging with the app Percentage of eligible participants and social supporters enrolled	Facility audits Study records
	Sustainability	Use of the app over time, social supporter engagement over time, and user retention Percentage of participants lost to follow-up and percentage of additional staff needed Qualitative: All, for example, what challenges did you experience or face while using this app?	Facility audits Study records Exit interviews
**Service outcomes**			
	Efficiency	Time spent on enrolling participants on the app, time spent on deliveries, timely delivery of needed supplementary or reference information, cost of delivery Qualitative: All, for example, what do you think about this intervention?	mHealth platform Exit interviews
	Effectiveness	Refer to aim 1	Refer to aim 1
	Equity	App use by facility type, participant type, and demographics	Study records
**Patient centeredness: accomplished during the formative and pilot work [36,60]**			
	Timeliness	Perceived impact on ANC attendance and skilled deliveries Qualitative: How was your experience attending ANC and preparing for birth and delivery?	Exit interviews
**Client outcomes**			
	Function	Perceived quality, impact on maternity care, use, and life (survey by Brazier et al [89]) Qualitative: How did this intervention help you in your pregnancy or work as an HCP?	Exit questionnaire Exit interviews
	Satisfaction	Satisfaction with intervention content, delivery, and credibility (Client Satisfaction Questionnaire) [93] for both HCPs and end users Qualitative: What concerns do you have about using this technology to support you?	Exit questionnaire Exit interview

^a^HCP: health care provider.

^b^mHealth: mobile health.

^c^HC: health center.

^d^ANC: antenatal care.

### Data Collection

#### Implementation Metrics

A trained RA will administer interviewer-led questionnaires at the trial exit (Table 4 presents outcomes and data sources) to (1) all intervention arm postpartum women, (2) all intervention arm social supporters, (3) all HCPs from participating facilities who enroll and deliver participants within the study sites, and (4) MOH key stakeholders and managers expected to inform rollout and adoption by the MOH. We will use a standardized checklist to conduct facility audits during implementation to document ANC visits and deliveries registered; maternity admission data; maternal mortality; disease cases managed; prescription data; laboratory data; and resource allocations at baseline, 12, 24, and 36 months following the implementation of the intervention for all study sites. A facility inventory will be done to inform our understanding of baseline conditions and set up for maternity and reproductive health services at the hospital and HC4 and HC3 public maternity centers.

We will use quantitative data on reported acceptability, appropriateness, effectiveness, function, and satisfaction to purposively select a subset of up to 15 postpartum individuals for exit in-depth interviews (or until saturation is met [94]), 15 social supporters, and up to 10 HCPs (approximately 2 for each facility level or district; refer to Table 1) involved in participant app enrollment and facility deliveries to clarify or contextualize observed outcomes based on the framework by Proctor et al [66] as outlined in Table 4. We will ask participants to describe actual events and experiences wherever possible (eg, for postpartum individuals, what worked well or poorly with receiving the messages and the challenges experienced during the study) to not only ensure coverage of specific areas but also allow unanticipated themes to emerge. We will further explore the feasibility, appropriateness, acceptability, patient centeredness, and sustainability of involving social networks in this intervention, as well as relationship dynamics, which have been shown to influence social supporter interventions [23-25] (eg, the social supporter’s specific role, their relationship throughout pregnancy, routine communication, the type of voluntary and requested SS given or received during pregnancy toward improving her experience, ANC visits, birth preparedness, childbirth, and the app-related challenges and opportunities). We will schedule these interviews between 4 and 6 weeks post partum. HCPs will also be interviewed at the end of the study to clarify potential opportunities and problems that were experienced with the intervention and its delivery. These will facilitate appropriate conclusions about effectiveness and implementation success.

#### Implementation Strategy Development

Using CFIR, we will develop guides to further interview these postpartum individuals, social supporters, and HCPs on the intervention, individual, and inner settings to inform our implementation strategies and optimize intervention delivery (Table 3). We will develop some initial implementation strategies based on these findings and the literature (eg, awareness campaigns in the community and dissemination or publicizing the app, implementation in facilities through local champions within or around each facility to maintain enrollments, training, choice of messaging format, automation, and routine audits with technical support as needed). At the end of the implementation period, we will present data on outcomes and cost-effectiveness of the framework by Proctor et al [66] (refer to aim 3), along with the preliminary implementation strategies to the facility, district, and national MOH managers and stakeholders who have key roles in budgeting and policy or service implementation and are expected to evaluate or endorse the app. Using CFIR-informed interview guides (Table 3), we will interview 5 to 10 of these key MOH managers and stakeholders for feedback and refine our initial implementation strategies for testing in a subsequent study. All qualitative interviews will be audiotaped with the participant’s permission and transcribed verbatim. RAs will be trained on the interview guides. All HCP and MOH interview guides will be piloted with 3 staff managers at Mbarara Hospital to ensure optimization, comprehension, and appropriateness.

### Intervention Fidelity

Intervention fidelity plays a key role in assessing intervention effectiveness [95,96]. An RA will ensure participants know how to use the phone to retrieve information. CHWs and HCPs from the targeted public HCs will be trained to enroll participants onto the app, with technical support from the study research teams, led by [name] and [name]. We will measure the 3 elements of implementation fidelity as outlined in Table 4. Notably, 13% of the women enrolled in our pilot study missed some app messages because of lost phones or phone functionality issues. To minimize dead battery and charging issues, solar chargers will be given to study participants to charge their phones as needed during enrollment. These chargers are readily available and inexpensive, and we will be tracking their cost. Phone losses will be assessed on a case-by-case basis, replaced sparingly, and costs will be determined accordingly. Outgoing SMS and voice messages will be monitored daily by the data management team. The times and lengths of individual outgoing calls and engagements will be recorded and transmitted to the server. Message deliveries during periods of inadequate cellular reception will be stored for later transmission. Although 2-way messaging has been found to be useful in other settings [11,14], our key factors in this proposal are to provide scheduled, targeted information and catalyze SS for women seeking maternity care, a mechanism that showed promising results in our pilot preliminary data. Moreover, 2-way messaging creates a burden on the health system that may not be sustainable. However, we will assess the need for this type of feature in the exit interviews for further exploration. In addition, contact numbers of the VHT and CHWs attached to the neighboring public HC will be provided to address any questions, referrals, or emergencies that may arise. SMS and voice call delivery or reception will be considered as proxies for accessing information to alter existing predisposing factors (such as negative health beliefs and low awareness) that could enable and improve perceived need to seek care with the help of available social networks, factors that will be assessed during exit interviews (Table 2 presents more details).

All quantitative data will be collected using a web-based database that will be developed in REDCap to improve data completeness, management, and quality control monitoring. Errors or out-of-range entries are reported immediately on the website so the original interviewer can reconcile the problem in a timely manner. Data entry verification will include algorithms that automatically check completed forms for missing, out-of-range, or inconsistent values before a form can be saved on the website.

